### Data Management and Statistical Analyses

Data from the competency checklists, completed by raters on the research team, and data from the self-reported evaluation completed by participants are collected via REDCap, which is CAMH’s designated web-based application for research data capture and then exported to Excel (Microsoft Corp) spreadsheets [31]. After data cleaning, these spreadsheets will be imported to a statistical software package (eg, SPSS, R) for analysis.

Testing of the 3 hypotheses will be done using repeated measures ANOVA. In addition, the study participants will be compared to all attendees in terms of their role and department to evaluate whether there are any striking differences despite our randomization methods. We also plan to assess the association between the frequency of physical skills used in the past month and our measures of skill competence, mastery, retention, confidence, and satisfaction.

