**Methods:**

We are using a pragmatic randomized controlled trial design. New staff registering for their mandatory safety training are randomly assigned to sessions which are, in turn, randomly assigned to either the BST or TAU conditions. Attendees are informed and consented into the study at the beginning of training. Differences between those consenting and those not consenting in terms of role and department are tracked to flag potential biases.

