## Methods

### Design, Setting, and Recruitment

Because we are interested in comparing the effectiveness, rather than the efficacy, of the two training methods, we are using a pragmatic randomized controlled trial (RCT) design. The study setting is a large mental health hospital in Ontario, Canada, which delivers inpatient, outpatient, and emergency health care across a wide range of patient populations.

Newly hired staff that are classified as clinical direct service staff must undergo 2 weeks of onboarding, which includes the trauma-informed de-escalation education for safety and self-protection (TIDES) program. Within those 2 weeks, physical skills training is a full-day, in-person session scheduled on the last day. Because the onboarding is tightly scheduled, there is limited time for the typical processes of providing information about the study, gaining agreement and informed consent, and randomization. Consequently, the following procedures have been introduced.

Prior to the 2-week onboarding training, all newly hired clinical direct-service staff will be randomly assigned to their physical skills training session, and the physical skills training sessions will be randomly assigned to either BST or TAU. On the day before the physical skills session, the study will be introduced by a research team member to all attendees at the end of the last session on the previous day; during that introduction, consent will be obtained via a WebEx poll to send interested attendees a copy of the informed consent, and all attendees will be informed that a question-and-answer session along with obtaining informed consent will be carried out before the start of the physical skills session the next day, and then the informed consent form will be emailed to those who provided permission.

Just before the physical skills session, questions about the study or informed consent will be answered, and one-on-one meetings will be conducted with each attendee in a separate room to further review the informed consent and to sign indicating whether they agree or decline to participate in the study. This procedure is designed to protect against attendees identifying who is involved in the study (hereafter “study participant”) and who is not (hereafter “trainee”).

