### Sample and Sample Size

Potential study participants include all newly hired clinical staff attending the mandatory training. There are no exclusion criteria (except the attendee’s desire not to be a study participant).

There is no published information on the expected effect size of BST versus other training methods. Indeed, most of the published BST studies have focused on efficacy and consequently have involved relatively small sample sizes. Consequently, we have opted for a sample size of 80 participants total (ie, 40 each in the BST and TAU groups) consistent with sample sizes providing 80% power for an expected medium to large effect size [25].

Recruitment began in January 2021, after REB approval was received. We reached our recruitment goal in September 2021.

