### Interventions

Both the TAU and BST methods teach the same skills for protecting a person against aggression (eg, someone attempting to punch or choke the staff member) as well as to help a team of staff members physically restrain a patient who is becoming an increased risk of harm to self or others. There are 11 target skills (6 for self-protection and 5 for team-control) that are mandatory for all newly hired staff (Textbox 1). Each skill has a number of defined components, and the same sequence of steps is followed to teach each component. However, the 2 training methods differ in how these steps are administered and monitored (Table 1). The BST protocol involves attendees actively performing the targeted skills through a loop involving instruction, modeling, practice, and feedback using competency checklists [20]. This is continued until the competency of the target skill is demonstrated based on the observation of the trainer [20]. While the common practice as described in the literature is for the attendee to demonstrate successful performance of a skill 2 to 3 times before moving to the next skill on the checklist [26], we have chosen a more stringent threshold of requiring correct execution 5 times consecutively with the expectation that this will further consolidate skill acquisition and possibly retention. In contrast, TAU does not assess competency or require trainees to reach a specific level of competence for a skill before moving on to the next skill. It does, however, include modeling, practice, and feedback.

Each training session is run by 2 facilitators, each training half of the attendees to make the most efficient use of the allotted time. To be compliant with COVID-19 restrictions at the time of the study on the numbers of in-person attendees (maximum of 10 individuals including the trainer), 1 trainer is present at the session, while the other delivers the same material virtually.

List of 11 target skills.

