The checklists (see self-protection checklist example, Multimedia Appendix 1) will be used during training for the BST sessions and for the baseline, posttraining, and 1-month study assessments for all study participants. On the training day, attendees will be asked individually to go to a separate room. They will be asked once to demonstrate each of the 11 skills prior to the start of training for baseline and just after the training for posttraining. Only those attendees who have consented to be study participants will have their baseline and posttraining assessments videotaped. For the 1-month follow-up, study participants will be asked to come in to have their skills assessed and videotaped. Videotaping will be done through WebEx (Cisco) and will be rated by a research team member using the predefined competency checklists. On these checklists, each skill component will be judged to be performed “correctly” or “incorrectly.” The final competency rating for each skill will be the percent of its component skills that were rated as correctly performed.

The reliability and validity of these ratings will be assessed using IOA calculations [28]. Prior to the study, raters had been trained on a test set of videotapes drawn from a previous study and had reached agreement levels of at least 90% for self-protection and team-control skills. For this study, all videotapes are rated by a primary rater. At the same time, a 30% random sample of videotapes from training months 1, 3, 4, 6, and 9 will be independently rated by a designated secondary (reliability) rater. IOA with the ratings from the primary rater will be calculated after every 2 videotapes rated by the secondary rater and, if the IOA is less than 90%, a recalibration discussion is held and recorded between the 2 raters with a third neutral rater available if needed to resolve any remaining differences. Recalibration decisions are then applied to all subsequent videotape ratings.

A predetermined threshold of 80%, consistent with clinical practice [29,30], is then applied to each competency rating to define skill mastery. Retention between posttraining and the 1-month follow up is measured in terms of whether the competency ratings changed as well as whether the percentage of study participants meeting the mastery threshold has changed.

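### Sessions, not individuals, are allocated to BST or TAU, but the repeated measures ANOVA named for all three hypotheses has no session term, so any post-training correlation within sessions makes its p-values too small

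*Protocol article*

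**What the plan says.** **Allocation.** The abstract's Methods paragraph says that new staff are "randomly assigned to sessions which are, in turn, randomly assigned to either the BST or TAU conditions". Design, Setting, and Recruitment repeats the second step: "the physical skills training sessions will be randomly assigned to either BST or TAU". Everyone attending a session is therefore in the same arm.

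**Delivery.** Under Interventions: "Each training session is run by 2 facilitators, each training half of the attendees". One trainer is in the room and the other teaches by video link. In-person numbers are limited to a "maximum of 10 individuals including the trainer".

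**Timing.** Skills are assessed "prior to the start of training for baseline and just after the training for posttraining" (Variables Assessed), and again at 1 month.

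**Sample size.** Under Sample and Sample Size: "we have opted for a sample size of 80 participants total (ie, 40 each in the BST and TAU groups"), described as "consistent with sample sizes providing 80% power for an expected medium to large effect size". No design effect, ICC or number of sessions is given.

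**Analysis.** Data Management and Statistical Analyses states: "Testing of the 3 hypotheses will be done using repeated measures ANOVA". The article names no session or facilitator term, and the Discussion does not list clustering among the limitations.

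**The concern.** In a repeated measures ANOVA with arm as the between-person factor, the repeated factor deals with correlation within a person. Differences between arms are judged against variation between people, as if each person had been allocated separately. Here the session was allocated. If people trained together finish more alike than people trained on different days, part of the session-to-session variation is counted as evidence about arm.

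There are reasons to expect such correlation. The outcome is a taught physical skill, the teaching is shared, 5 of the 11 skills are team controls, and Table 1 leaves repetition in TAU to the instructor. Baseline precedes training and the other two assessments follow it, so a session effect that arises in training goes straight into the group-by-time contrast.

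The error runs in one direction: p-values too small and intervals too narrow. The same test is named for competence, mastery, retention and confidence. The authors expect BST to do better and intend the results to shape the hospital's training, so a false positive would have consequences.

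**Working it through.** **Inputs from the article:** 40 per arm; session as the unit allocated to arm; one assessment before training and two after.

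**Assumptions (not in the article):** two-sided 5% test; *m* = 5 or 8 participants per cluster, in keeping with the in-person cap; post-training ICC of 0.01 to 0.20. With 40 per arm, *m* = 5 means 8 sessions per arm and *m* = 8 means 5 per arm.

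**Step 1: the article's own figure.** For two independent groups of 40, a t test has 80% power at d = 0.634. The normal approximation gives 80.4% at d = 0.63. At d = 0.5, power is 61% (63 per arm needed for 80%); at d = 0.8 it is 95% (25 per arm needed). So 40 per arm does fit an effect between medium and large, but as a calculation for independent individuals.

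**Step 2: design effect and true error.** DE = 1 + (*m* − 1) × ICC. An analysis that omits the session has true error 2 × [1 − Φ(1.96/√DE)]. For *m* = 5 and ICC 0.10: DE = 1 + 4 × 0.10 = 1.40, 1.96/√1.40 = 1.66, error 9.8%.

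**Step 3: simulation of the named test.** The group-by-time F test was simulated with no arm effect (4,000 trials per setting, three time points, within-person correlation 0.5, session effect arising only after training).

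**Step 4: power of an analysis that allows for session**, at d = 0.634: Φ(0.634 × √(40/(2 × DE)) − 1.96). This is for a single comparison of means, without gain from baseline adjustment or loss from few degrees of freedom.

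| *m* | ICC | DE | Error, formula | Error, simulated | Power |
|---|---|---|---|---|---|
| 5 | 0.01 | 1.04 | 5.5% | not run | 79% |
| 5 | 0.05 | 1.20 | 7.4% | 7.2% | 74% |
| 5 | 0.10 | 1.40 | 9.8% | 10.0% | 67% |
| 5 | 0.20 | 1.80 | 14.4% | 14.8% | 56% |
| 8 | 0.01 | 1.07 | 5.8% | not run | 78% |
| 8 | 0.05 | 1.35 | 9.2% | 7.9% | 69% |
| 8 | 0.10 | 1.70 | 13.3% | 13.1% | 59% |
| 8 | 0.20 | 2.40 | 20.6% | 22.2% | 45% |

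At ICC 0 the simulated error was 5.0% for both cluster sizes.

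**Step 5: half-session clusters.** If the trainer is the main source of correlation, *m* is 2.5 to 4. The formula then gives 5.9-6.8% at ICC 0.05 (DE 1.075 to 1.15) and 6.8-8.6% at ICC 0.10 (DE 1.15 to 1.30).

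**Step 6: which remedies work.** Comparing session means of the change score kept the error at about 4-7% in simulation. Adding only a session intercept that is constant over time did not help the group-by-time test. A constant term cancels from within-person change, so in balanced data the F test is the same as without it. Simulated error with that model was 9-13% at ICC 0.10 and up to 23% at ICC 0.20.

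**The case against.** **Staff are also randomised to sessions.** This is the best defence, and it stands for baseline: sessions should not differ systematically before training. It does not make outcomes independent after people have been taught together.

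**The article never says that clustering is ignored.** True. It is a condensed report with one sentence on the test, an ANOVA can carry session nested in arm, and model terms are often left to an analysis plan. What stands is narrower: the test is named, no session term is named with it, and the sample size is stated as for independent individuals. As written, the method does not fit the allocation.

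**Shared trainer.** A reader might infer that everyone in a session has the same trainer and delivery mode. The article does not support that: each facilitator takes half of the attendees, one in person and one by video. What the whole session shares is the day, the peers and the arm; each half shares a trainer. The effective cluster may therefore be smaller than a session. It could also be larger if trainers recur across sessions, which the article does not say.

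**Unknown ICC.** A reader might take the upper error rates as established. They are not. No ICC is given, training to a criterion in BST could make session variation differ by arm, and near ICC 0.01 the error is only 5-6%.

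**Conclusion.** The point holds as a mismatch between the unit allocated and the test named, and should be corrected before analysis. For any positive post-training ICC the named test is too liberal. How much is not known from the article: from almost nothing at ICC 0.01 to 14-22% at ICC 0.20 with clusters of 5 to 8, and about 6-9% at ICC 0.05-0.10 if the cluster is half a session. Cluster sizes and ICCs are assumptions throughout. The documents do not support a claim that the trial's error rate is any particular figure, or that the investigators have decided to disregard sessions. A further tempting inference, that adding a random session intercept to the planned three-time-point model would be enough, is also wrong if the session effect arises in training.

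**What to change.** Replace the ANOVA with an analysis that takes session as the unit of inference for post-training outcomes. Either:

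- (a) compare baseline-adjusted session means, or use a permutation test over sessions, which suits a small number of sessions; or
- (b) fit a mixed model to the posttraining and 1-month scores with baseline as a covariate, a random session effect and small-sample degrees of freedom (Kenward-Roger or Satterthwaite). If baseline is kept as an outcome, use a random session-by-time effect.

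Treat the mastery and confidence percentages in the same way, for example as session-level proportions. Report the number of sessions per arm and the ICC. Facilitator half within session can be a further term if it was recorded, which the list of variables does not show. A delivery-mode term and an unstructured within-person covariance are optional.

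**Cost.** Recruitment is complete, so N is fixed. The article says that analysis had not begun as of May 2022. No new data are needed provided session membership can be recovered from the allocation. Intervals will be wider, and power at d = 0.63 falls to about 67-74% (clusters of 5) or 59-69% (clusters of 8) for ICC 0.05-0.10. Few sessions lower it further: with 16 or 10 sessions, a comparison of session means has 14 or 8 degrees of freedom, against 78 for 80 independent people. The report should say so and not repeat the 80% figure.

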There is a large body of evidence that indicates that individuals who receive BST demonstrate significant improvement in targeted skills posttraining and maintain those skills over time and across settings [21-23]. This model has been used to train a wide range of participants including behavior analysts, parents, and educators to build safety-related skills and manage aggressive behavior [21,24].

The objective of this study is to compare the real-world effectiveness of BST and TAU in terms of physical safety skills acquisition and retention after 1 month as well as staff confidence in their use of these skills.

The following are the null hypotheses being tested: there will be no significant differences between BST and TAU in terms of (1) the competence scores or the percentage of study participants who attain mastery (predefined as a score of 80% or higher) for self-protection or team control physical skills at the end of the mandated training session; (2) the competence scores or the percentage of study participants that continue to demonstrate mastery at 1 month posttraining for either self-protection or team-control skills (retention); and (3) the percentage of study participants who express confidence in their skills at 1 month posttraining.

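### One repeated measures ANOVA is named for three hypotheses that are arm differences at specific visits, partly on percentages; its standard tests do not match them and do not use baseline as a covariate

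*Protocol article*

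**What the plan says.** The Introduction sets three null hypotheses, each tied to a visit.

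- Hypothesis 1 compares competence scores or the percentage at mastery "for self-protection or team control physical skills at the end of the mandated training session".
- Hypothesis 2 compares competence scores or "the percentage of study participants that continue to demonstrate mastery at 1 month posttraining".
- Hypothesis 3 compares "the percentage of study participants who express confidence in their skills at 1 month posttraining".

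Under Variables Assessed, the checklists are used "for the baseline, posttraining, and 1-month study assessments for all study participants". Baseline precedes any training: "They will be asked once to demonstrate each of the 11 skills prior to the start of training for baseline". The last assessment is a separate return visit: "For the 1-month follow-up, study participants will be asked to come in to have their skills assessed and videotaped". The same section defines retention as a change: "Retention between posttraining and the 1-month follow up is measured in terms of whether the competency ratings changed", together with the change in the percentage at mastery.

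Data Management and Statistical Analyses then gives one sentence on method: "Testing of the 3 hypotheses will be done using repeated measures ANOVA". It names no visits, no term or contrast of interest and no role for baseline.

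**The concern.** A repeated measures ANOVA with two arms yields a group effect (averaged over visits), a time effect and a group-by-time effect. None of these is an arm difference at one visit, which is what each hypothesis asks about.

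Hypothesis 1 shows the problem most clearly. It concerns one visit, but a repeated measures model needs at least two, so another visit must be brought in.

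- **Baseline added.** A score that training cannot affect becomes an outcome instead of a covariate.
- **1 month added.** The group effect mixes hypotheses 1 and 2, and the collected baseline is not used.
- **Both added.** The group effect is diluted by baseline and mixes the two later visits.

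The main stake is interpretation. The trial asks whether BST improves acquisition, retention or both, and a significant omnibus F does not separate these. The second stake is power, because baseline adjustment does better in every scenario examined. Third, an ANOVA of scores is not a natural test of the percentage at mastery or the percentage confident.

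**Working it through.** **Inputs.** From the article: 80 participants, 40 per arm; 80% power for a medium to large effect; assessments at baseline, posttraining and 1 month. Assumed, because the article gives no figure: two-sided 5% level, SD 1 at each visit, equal correlation r between visits, conventional values of 0.5 (medium) and 0.8 (large), and 10 to 30% loss at 1 month. Participants are treated as independent.

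**1. The stated sample size.** A two-sample t test with 40 per arm has 80% power at d = 0.634. Power is 60% at d = 0.5 and 94% at d = 0.8. So 80 participants is consistent with a medium to large effect, and d = 0.634 is used below.

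**2. Size of the group effect.** With arm differences of 0, 0.634 and 0.634 SD at the three visits, the group effect estimates (0 + 0.634 + 0.634)/3 = 0.423 SD, two-thirds of 0.634.

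**3. Power when the effect is present at both later visits.**

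- Group effect: the mean of three visits has variance (1 + 2r)/3, so the standardized effect is 0.423/√((1 + 2r)/3). This is 0.619, 0.546 and 0.494 for r = 0.2, 0.4 and 0.6.
- Group-by-time: F on 2 and 156 df with noncentrality 20 × S/(1 − r), where S is the sum of squared deviations of the arm differences from their mean. S = 0.268, so the noncentrality is 6.70, 8.93 and 13.40.
- Baseline-adjusted contrast at one visit: standardized effect 0.634/√(1 − r²), which is 0.647, 0.692 and 0.793.

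| Test | r = 0.2 | r = 0.4 | r = 0.6 |
|---|---|---|---|
| Group effect, three visits | 78% | 67% | 59% |
| Group-by-time, three visits | 63% | 76% | 91% |
| Baseline-adjusted contrast | 82% | 86% | 94% |

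If only baseline and posttraining entered, group-by-time would be a change-score test with standardized effect 0.634/√(2(1 − r)). Its power is 60%, 73% and 88%, still below the adjusted contrast.

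**4. What a rejection means.** Place the 0.634 SD effect at only one later visit, with r = 0.5. S is again 0.268 and the noncentrality is 20 × 0.268/0.5 = 10.7. In 5,000 simulated trials per scenario, group-by-time rejected 83% of the time when the effect was at 1 month only, although the arms did not differ at the end of training. The baseline-adjusted posttraining contrast rejected 5%. With the effect at posttraining only, group-by-time again rejected 83%, although the arms did not differ at 1 month.

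**5. If the classical complete-case ANOVA is used.** Anyone who misses the 1-month visit also leaves the posttraining comparison. Loss of 10, 20 or 30% leaves 36, 32 or 28 per arm. Two-sample t-test power at d = 0.634 falls from 80% to 76%, 70% or 64%. This shows the cost of the lost participants; it is not the power of the ANOVA itself.

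**The case against.** The strongest reply is that the article gives one sentence on method and leaves detail to a plan that is not shown. Several points in that reply stand.

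- **Visits.** The article does not say that all three enter the ANOVA. That is inferred from the assessment schedule.
- **Tests neither hypothesis.** A reader might infer this, but it goes too far. Visit-specific contrasts can follow a repeated measures ANOVA. A group-by-time term on posttraining and 1 month alone directly tests differential retention, as Variables Assessed measures it, with 80% power at r = 0.5 if a 0.634 SD effect has vanished by 1 month.
- **Missed visits.** A reader might also infer that anyone who misses the 1-month visit will be dropped. That is true of the classical method, but the article states no missing-data rule, gives no attrition figure and leaves the software open.
- **Bias toward zero.** This applies only if the group effect over visits including baseline is reported as the result. Group-by-time is the more usual term, and at r = 0.6 its power (91%) is close to the adjusted contrast (94%). Leaving baseline out as a covariate costs efficiency in a randomized comparison; it does not invalidate a test.

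The reply does not remove the mismatch. The article does fix a method for all three hypotheses, and no choice of visits makes its standard tests an arm contrast at one visit. The percentage outcomes are assigned to the same ANOVA.

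**Conclusion.** The point holds in a limited form: the named method is poorly matched to the stated hypotheses, and a better-matched one is available from the same data. The firm part is that the group and group-by-time tests are not the visit-specific comparisons in the Introduction and do not suit its percentages.

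The sizes are conditional. The two-thirds dilution and the 78/67/59% and 63/76/91% powers require all three visits as outcomes, d = 0.634 at both later visits and the assumed correlations. The fall to 76/70/64% requires complete-case analysis and the assumed losses. At high correlation the power loss of the interaction test is small, and the fault is mainly that it does not locate the difference. The documents do not support saying that the hypotheses go untested or that participants will be excluded. All figures ignore any correlation within training sessions.

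**What to change.** Replace the ANOVA sentence under Data Management and Statistical Analyses as follows.

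- **Competence scores.** Fit a linear mixed model to the posttraining and 1-month scores, with baseline score as covariate and arm, time and arm-by-time as fixed effects. Use all participants with at least one postbaseline score. Test hypothesis 1 by the arm contrast at posttraining and hypothesis 2 by the arm contrast at 1 month. Report the arm-by-time term as the test of differential retention.
- **Percentages.** For mastery (hypotheses 1 and 2) and confidence (hypothesis 3), use a baseline-adjusted binary model, for example logistic, at the named visit.

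The cost is wording and slightly more analysis work. Baseline skill and confidence are already collected. N=80 need not change for this point: before attrition, the adjusted contrast has at least the planned 80% power at d = 0.634. The Results section reports data collection complete but analysis not begun as of May 2022, so at that stage the contrasts could still be fixed before results were seen.
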